**Methods and analysis:**

This is a prospective, multicenter, randomized, sham-controlled trial. A total of 156 participants with PCOS will be randomly assigned at a 1:1 ratio to receive either manual acupuncture (MA) or sham acupuncture (SA). Eligible participants present with spontaneous menstrual cycles lasting 35–60 days and a body mass index (BMI) below 28.0 kg/m², and this trial targets a subgroup of patients with mild-to-moderate ovulatory dysfunction. The intervention lasts 12 weeks and comprises 36 treatment sessions (three sessions weekly), after which participants will enter a 12-week follow-up phase. The primary outcome is the cycle ovulation rate (COR) at Week 12, verified via transvaginal ultrasound. Secondary outcomes include menstrual cycle characteristics, reproductive hormone profile, metabolic parameters, anthropometric measures, quality of life, anxiety and depression, patient global impression of change, and safety outcomes. Intention-to-treat analysis will be performed, and a p-value <0.05 (two-sided) will be defined as the threshold for statistical significance.

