### Inclusion criteria

2.3

Participants will be women diagnosed with polycystic ovary syndrome (PCOS) according to the 2003 Rotterdam criteria (4), after the exclusion of other potential causes of hyperandrogenism or anovulation (e.g., thyroid dysfunction, hyperprolactinemia, congenital adrenal hyperplasia, androgen-secreting tumors). Eligible participants must meet all of the following criteria: (1) aged 21–40 years old; (2) maintained spontaneous menstrual cycles (without hormonal ovulation induction) over the preceding 12 months, with consistent cycle lengths ranging from 35 to 60 days; and (3) provision of written informed consent.

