### Intervention

2.7

All acupuncture treatments will be administered by licensed acupuncturists with a minimum of 2 years of clinical experience who have completed standardized protocol training. Treatment will commence within 2–4 days of the onset of a spontaneous menstrual period following enrollment. The intervention lasts for 12 weeks, with sessions administered three times per week (every other day), totaling 36 sessions.

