### Outcome measurement

2.9

All outcome measurements will be scheduled according to the study timeline (**Table 1**). Baseline assessments will be performed before randomization and prior to the first treatment. Primary and secondary outcomes are assessed at the end of the 12-week treatment period (Week 12) and at the end of the 12-week follow-up period (Week 24).

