#### Primary outcome

2.9.1

The primary outcome is the cycle ovulation rate (COR). To account for the inherent irregularity of menstrual cycles in PCOS, the 12-week treatment period is divided into three standardized 28-day (4-week) time windows (i.e., Weeks 1-4, 5-8, and 9-12), each serving as an observation unit for detecting ovulation. COR is calculated using the following formula: COR (%) = (Number of 28-day time windows with ultrasound-confirmed ovulation/Number of completed full 28-day time windows) × 100% (19, 20). For participants who complete the full 12-week treatment period, the denominator is 3. For participants who withdraw early, the denominator is the number of full 28-day time windows completed before withdrawal. Participants who complete at least one full 28-day time window will be included in the primary analysis. Ovulation is confirmed by transvaginal ultrasound (TVUS), which serves as the gold standard. A window is considered ovulatory when TVUS documents the development of a dominant follicle (≥18 mm in diameter) followed by its subsequent collapse or disappearance, accompanied by the appearance of free fluid in the pouch of Douglas (29). Given that women with PCOS often have prolonged and irregular menstrual cycles, urinary LH test strips will be used daily to optimize the timing of ovulation monitoring. For each menstrual cycle, testing will begin on day 10–12 of that cycle and continue until ovulation is confirmed or the cycle ends. Once a positive LH test is observed, transvaginal ultrasound will be performed to confirm follicular rupture and ovulation. For participants who do not achieve a positive LH test, daily LH test strip use will continue until the end of that menstrual cycle. Daily basal body temperature (BBT) charting will be maintained as a supplementary record.

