#### Secondary outcomes

2.9.2

Menstrual cycle characteristics will be evaluated using two measures: 1) mean menstrual cycle length, calculated as the total number of days in the observation period (84 days for the 12-week treatment period, and 84 days for the 12-week follow-up period) divided by the number of menstrual cycles that occurred during that period. A menstrual cycle is defined as the interval from the first day of one menstrual bleeding to the day before the next menstrual bleeding. If no menstrual bleeding occurs during the entire observation period, the mean cycle length is considered missing, and the participant will be classified as having amenorrhea for that period. This value will be derived from participant-maintained calendars, and the average during treatment and follow-up will be compared to the self-reported baseline.; and 2) the menstrual cycle recovery rate, defined as the proportion of participants achieving a normalized cycle length of 21–35 days.

The sex hormone profile, measured in the early follicular phase (days 2–5 of a spontaneous cycle), includes the Free Androgen Index (FAI) (calculated as [total testosterone/sex hormone-binding globulin (SHBG)] × 100) (30) and the LH/FSH ratio.

The metabolic profile comprises three domains: 1) Anthropometric measures: body weight, height (for BMI), waist circumference (WC), and hip circumference (HC) to calculate the waist-to-hip ratio (WHR); 2) Glucose metabolism: fasting plasma glucose (FPG) and fasting insulin (FINS), with insulin resistance estimated by the Homeostatic Model Assessment index (HOMA-IR), a marker of insulin resistance, is calculated as (FINS × FPG)/22.5 (31); 3) Lipid profile: Total cholesterol (TC), triglycerides (TG), high-density lipoprotein cholesterol (HDL-C), and low-density lipoprotein cholesterol (LDL-C).

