### Statistical analysis

2.13

All analyses will adhere to the Intention-to-Treat (ITT) principle. The baseline characteristics will be summarized descriptively by group using means (standard deviations) or medians (interquartile ranges) for continuous variables and frequencies (percentages) for categorical variables to assess between-group comparability.

For the primary outcome, the cycle ovulation rate (COR) at Week 12, any missing data will be handled using multiple imputation by chained equations (MICE) with 20 imputed datasets, and results combined using Rubin’s rules (35). The COR will be compared between groups using a linear mixed-effects model with study center as a random effect. The result will be presented as the mean difference between groups with its 95% confidence interval. As a sensitivity analysis, a per-protocol (PP) analysis will be performed, including only participants who completed the 12-week intervention with adequate adherence (defined as receiving ≥80% of the scheduled acupuncture sessions) and without major protocol violations.

To assess the sustainability of the treatment effect, the COR at Week 12 and Week 24 will be analyzed together using a linear mixed-effects model for repeated measures, including group, time point (Week 12, Week 24), and group-by-time interaction as fixed effects, with study center and participant as random effects (36).

The analyses for secondary outcomes will be conducted using available data. Continuous outcomes will be analyzed using Analysis of Covariance (ANCOVA), adjusting for corresponding baseline values and study center (37). Binary outcomes will be analyzed using generalized linear mixed models, incorporating study center as a random effect (38). All statistical tests will be two-sided, and a p-value < 0.05 will be considered statistically significant. All analyses will be performed using SAS software (version 9.4, SAS Institute Inc., Cary, NC, USA).

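### Week 12 and Week 24 COR are not like for like, because only the treatment windows start at a menses; the time and group-by-time terms can therefore shift, in either direction, with no change in ovulation.

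*Protocol article*

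**What the plan says.** All references are to the protocol article.

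- **Start of treatment (2.7):** "Treatment will commence within 2–4 days of the onset of a spontaneous menstrual period following enrollment".
- **Observation unit (2.9.1):** "the 12-week treatment period is divided into three standardized 28-day (4-week) time windows". COR is the ratio "Number of 28-day time windows with ultrasound-confirmed ovulation/Number of completed full 28-day time windows".
- **Follow-up (Abstract, 2.9, Table 1):** treatment lasts 12 weeks, "after which participants will enter a 12-week follow-up phase", and COR is assessed again at Week 24. Section 2.9.2 gives "84 days for the 12-week follow-up period" as the observation length, though only for mean cycle length. No section ties the start of follow-up to a menses.
- **Population (2.3):** women "with consistent cycle lengths ranging from 35 to 60 days".
- **Sustainability model (2.13):** a repeated-measures linear mixed model for COR at both time points, "including group, time point (Week 12, Week 24), and group-by-time interaction as fixed effects".

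**The concern.** Every woman enters Week 1 at the start of a cycle, well before her next ovulation. She enters Week 13 at whatever cycle day she has then reached. With cycles longer than the 28-day window, the starting phase determines how many ovulations an 84-day span can hold. The expected COR of the two periods can therefore differ when nothing about ovulation has changed.

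A phase shift common to both arms goes into the time effect. A shift that differs by arm goes into the group-by-time term, which is the natural place to look for loss or persistence of effect. Cycle length drives the shift and is itself an outcome the trial hopes to change (2.9.2 counts recovery to 21–35 days), so the shift need not cancel between arms. The trial could report waning, a late gain, or a rise in the sham arm after treatment that is only cycle phase.

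**Working it through.** **The plan's own figure.** Section 2.12 anticipates 65% against 40%. With pooled variance, no continuity correction, two-sided α 0.05 and 80% power:

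n = [1.960·√(2·0.525·0.475) + 0.842·√(0.65·0.35 + 0.40·0.60)]² / 0.25² = 61.4, so 62 per group. Then 62/0.80 = 77.5, so 78 per group and 156 in total. This reproduces, and 65% and 40% serve below as calibration points.

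**Inputs from the article:** start 2–4 days after menstrual onset (2.7), 28-day windows (2.9.1), cycles of 35–60 days at entry (2.3), follow-up directly after Week 12 (Abstract).

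**Assumptions not in the article:** ovulation 14 days before the next menses; follow-up made up of three consecutive 28-day windows over Weeks 13–24; the same cycle process throughout all 24 weeks; cycle lengths spread evenly over the stated range.

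**Hand calculation, stable cycles, all ovulatory.** Let trial day 1 be cycle day 3 and L the cycle length. The k-th ovulation falls on trial day kL − 16. It lies in the treatment period if kL ≤ 100 (day 84) and within 24 weeks if kL ≤ 184 (day 168). As L exceeds 28, no window holds two ovulations.

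| Cycle length (days) | Ovulatory windows, Weeks 1–12 | Ovulatory windows, Weeks 13–24 |
|---|---|---|
| 35–36 | 2 | 3 |
| 37–46 | 2 | 2 |
| 47–50 | 2 | 1 |
| 51–60 | 1 | 2 |

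For example, L = 57 gives ovulations on days 41, 98 and 155, so COR is 1/3 and then 2/3. L = 48 gives days 32, 80 and 128 (the next is day 176), so COR is 2/3 and then 1/3.

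Averaged over the 26 whole-day lengths:
- Weeks 1–12: (16·2 + 10·1)/78 = 42/78 = 53.8%.
- Weeks 13–24: (2·3 + 10·2 + 4·1 + 10·2)/78 = 50/78 = 64.1%.
- Shift: +10.3 points with nothing changed.

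Simulation with 200,000 women per scenario and start days 2–4 gives 54.0% to 63.6%, or +9.6 points.

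**How far the shift moves with the assumptions (simulation):**
- All cycles ovulatory, 35–60 days: +8.9 points at a within-woman SD of 3 days, +7.7 at SD 5, +6.6 at SD 7, +5.4 at SD 10. It is −1.7 if every cycle is drawn independently from 35–60 days.
- Narrower ranges at SD 3: 35–45 days +4.7, 38–50 days −6.4, 40–55 days +0.7, 45–60 days +11.7.
- Calibrated to the 40% control COR (about 73–74% of cycles ovulatory): +7.1 at SD 0, falling to +4.8 at SD 7.

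**Group-by-time term, with an effect that is in truth fully sustained:**
- *Calibrated to 65% against 40% at Week 12, active arm with shorter cycles from the start (ranges from 28–35 to 30–50 days), SD 0–7.* The 25-point difference reads as about 13–20 points at Week 24, a bias of about −12 to −5 points.
- *Active treatment raises only the ovulation probability, cycles stay at 35–60 days.* The difference grows by about 2 to 3 points (for example 0.13 to 0.16 with 95% against 70% of cycles ovulatory). COR at Week 12 then cannot exceed about 54–55%.
- *Cycles 20% shorter, 90% against 70% ovulatory, SD 4.* With shortening from the first session the difference goes from 0.30 to 0.22. With shortening only from the next cycle it goes from about 0.21 to 0.23. With all cycles ovulatory the corresponding figures are 0.21 to 0.11, and 0.11 to 0.11.

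**The case against.** **The follow-up windows are inferred.** Section 2.9.1 defines windows for the treatment period only, and the full protocol or analysis plan may define Week 24 differently. This stands as a limit on the numbers. Consecutive 28-day windows are the natural reading, and nothing in the article suggests a restart at a menses.

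**A reader might infer a fixed artefact of about 10 points.** The documents do not support that. It needs stable, all-ovulatory cycles spread evenly over 35–60 days, and the article gives no cycle distribution. At its own 40% control rate the shift is 5–7 points, and it can be negative.

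**A reader might also infer that a sustained effect will look partly lost.** That does not follow either. A shift common to both arms enters only the time effect. The apparent loss needs shorter cycles in the active arm and, in the 20% scenarios, shortening that acts on the cycle already in progress; it largely disappears when shortening begins with the next cycle. A delayed onset is itself a real change over time, so this does not remove the artefact, but it makes the sign of the bias unpredictable.

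**The model is not wrong in itself.** Section 2.13 names no waning rule, and the same fit yields the Week 24 between-arm difference. This also stands: what needs fixing is which term carries the conclusion.

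**Conclusion.** The concern holds as a problem of comparability between the two periods. Treatment-period COR is locked to early cycle phase and follow-up COR, as described, is not, so a change from Week 12 to Week 24 mixes cycle phase with any change in ovulation. Under the stated assumptions the shift within an arm is several points: about 5–7 at a 40% control COR, up to about 10 in the simplest case, and about −6 to +12 over narrower cycle ranges. The bias in the group-by-time term is roughly −12 to +3 points against an anticipated effect of 25, with a direction that cannot be fixed in advance.

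The randomised Week 12 comparison is unaffected, because both arms start at a menses. The Week 24 between-arm difference remains a randomised contrast over one common calendar period; what cannot be interpreted is its change from Week 12. The point concerns a secondary conclusion, but one likely to be reported prominently, and should be addressed.

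**What to change.** In section 2.13, state that the sustainability conclusion rests on the between-arm COR difference at Week 24, reported as an estimate with 95% CI from the model already planned. Add that the time effect and the Week 12 to Week 24 change in the difference will not be read as waning or persistence.

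The share of cycles starting in each period that were ovulatory is not a ready substitute. It omits the first treated cycle, whose menses precedes treatment, and it counts late follow-up cycles whose ovulation falls after observation ends. In a simulation with all cycles ovulatory and SD 4, 36% of cycles starting in follow-up ovulate after Week 24, so the share falls from 1.00 to 0.64 with nothing changed. If used at all, it should be a descriptive supplement with explicit rules for the first treated cycle and for cycles incomplete at Week 24.

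Cost: wording only, with no new data and no new model. Downside: the trial gives up a formal test of change over time.

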### Sample size

2.12

The sample size calculation was based on the primary outcome, the cycle ovulation rate (COR). Based on a systematic review of prior studies (15, 19, 20) and our pilot data[Trial Registration Number: ChiCTR2300073494], we anticipated a COR of 65% in the MA group and 40% in the SA group at the end of the treatment. Using a two-sided Chi-square test with a significance level (α) of 0.05 and a power (1-β) of 80%, the required sample size per group was calculated to be 62 participants. Accounting for an estimated 20% dropout rate over the 24-week study period, the final target sample size was 78 participants per group, for a total of 156 participants. This calculation was performed using PASS software (version 15.0).

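### Continuous secondary outcomes measured at Weeks 12 and 24 are analysed by available-data ANCOVA, so Week 12 values do not inform the Week 24 comparison for women lost in between

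*Protocol article*

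**What the plan says.** The protocol article, Outcome measurement, states: "Primary and secondary outcomes are assessed at the end of the 12-week treatment period (Week 12) and at the end of the 12-week follow-up period". The second of these visits is at 24 weeks. Table 1 marks hormones, metabolic parameters, anthropometrics and the questionnaires at baseline and at both later visits. The Patient Global Impression of Change (PGIC) is marked at the two later visits only.

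Statistical analysis sets both the missing-data rule and the method for these outcomes: "The analyses for secondary outcomes will be conducted using available data. Continuous outcomes will be analyzed using Analysis of Covariance (ANCOVA". The covariates are the outcome's own baseline and the centre. No visit term, participant effect or imputation is given for them.

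The same section treats the cycle ovulation rate (COR) differently. At Week 12, "any missing data will be handled using multiple imputation by chained equations (MICE) with 20 imputed datasets". To judge whether the effect lasts, "the COR at Week 12 and Week 24 will be analyzed together using a linear mixed-effects model for repeated measures". The section opens with "All analyses will adhere to the Intention-to-Treat (ITT) principle". Sample size anticipates the loss: "Accounting for an estimated 20% dropout rate over the 24-week study period".

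**The concern.** ANCOVA takes one response per woman. On available data, the Week 24 analysis contains only women with a Week 24 value and adjusts for baseline and centre. It is unbiased if, given baseline, centre and arm, being missing at Week 24 is unrelated to the outcome. Treatment stops at Week 12, so whether a woman returns 12 weeks later could depend on how she was doing at Week 12. That value has been recorded, but the Week 24 analysis does not use it.

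At stake are the Week 24 group differences in hormones, metabolic measures, anthropometry, quality of life, anxiety and depression. They could be biased if dropout follows the Week 12 result differently in the two arms, and they are slightly less precise than they could be even if dropout is random. The method is named outright in the article, so this is a choice already made and not a detail left to an analysis plan.

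**Working it through.** **1. The plan's own figures.** Inputs from Sample size: 65% against 40%, two-sided α 0.05, power 80%, 20% dropout.

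n = [1.960·√(2·0.525·0.475) + 0.842·√(0.65·0.35 + 0.40·0.60)]² / 0.25² = (1.384 + 0.575)² / 0.0625 ≈ 61.4, so 62 per group. Then 62/0.80 = 77.5, so 78 per group and 156 in all. The stated figures reproduce.

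**2. Women affected at Week 24.** 156 × 0.80 = 124.8, about 125 with a value; 156 × 0.20 = 31.2, about 31 without. The 20% covers all 24 weeks. Women who leave before Week 12 have no Week 12 value to use, so 31 is the upper limit of those a joint model could help with.

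**3. Assumptions not in the documents.** Correlation with baseline r_b = 0.5; correlation between Weeks 12 and 24 r = 0.6 to 0.8; outcomes in SD units with higher meaning better; all loss after Week 12, or half of it.

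**4. Precision under random dropout.** The slope of Week 24 on Week 12 given baseline, which here is also their partial correlation, is ρ = (r − r_b²)/(1 − r_b²):

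- r = 0.6: 0.35/0.75 = 0.467
- r = 0.8: 0.55/0.75 = 0.733

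In large samples, variance of joint model / variance of ANCOVA ≈ 1 − fρ², where f is the share of women with a Week 12 value who lack a Week 24 value.

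- All loss after Week 12, f = 0.20: 1 − 0.20·0.218 = 0.956 and 1 − 0.20·0.538 = 0.892. The SE is 2.2% and 5.5% smaller.
- Half the loss before Week 12, f = 15.6/140.4 = 0.111: 0.976 and 0.940. The SE is 1.2% and 3.0% smaller.

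Simulated SEs with all loss after Week 12 (2,500 trials per scenario) were 0.155 against 0.152 (r = 0.6) and 0.156 against 0.145 (r = 0.8), that is 2% and 7% smaller. The 7% lies a little above the formula and partly reflects simulation error.

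**5. Bias under informative dropout.** ANCOVA bias ≈ ρ × (between-arm difference in how far dropout shifts the baseline-adjusted Week 12 mean of those who stay). Simulation with 78 per arm and a dropout logit slope of 1 per SD of the Week 12 value:

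| Dropout pattern | All loss after Week 12 | Half before Week 12 |
|---|---|---|
| Random | 0 | 0 |
| Poor responders leave both arms alike (no true effect) | about 0; false positives about 5% | not reported |
| Poor responders leave sham only | −0.06 to −0.10 SD | −0.04 to −0.05 SD |
| Poor leave sham, good leave active | −0.12 to −0.20 SD | −0.07 to −0.11 SD |

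The sham-only row fits the formula: 0.06/0.467 ≈ 0.13 and 0.10/0.733 ≈ 0.14, so one shift of about 0.13 to 0.14 SD explains both ends. With all loss after Week 12, joint-model bias was at most 0.01 SD.

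In the opposite-direction pattern with all loss after Week 12, the ANCOVA rejected a true null in 11% to 25% of trials across runs. Its power for a true 0.4 SD effect fell from about 72% to between 26% and 41%. With half the loss before Week 12, the false-positive rate was about 7% to 11%.

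**6. Separate check** (4,000 trials, true Week 24 effect 0.50 SD, dropout slope 1.2, r = 0.5 to 0.8, all loss after Week 12). Sham-only dropout: ANCOVA 0.39 to 0.45, joint model 0.50. Same dropout rule in both arms: ANCOVA 0.46 to 0.48, joint model about 0.50. Random dropout: both about 0.50, with joint-model variance 2% to 10% lower.

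**The case against.** Baseline-adjusted ANCOVA at one visit is a standard method, and it is valid if dropout is unrelated to the outcome given baseline, centre and arm. These are secondary outcomes, and the question of lasting effect is already answered for COR by a repeated-measures model. All of that stands, and it limits how much the point matters.

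A reader might also infer four stronger things that the documents do not support.

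- *Week 12 data are thrown away.* They are not. They enter the Week 12 comparison and are unused only in the Week 24 one.
- *The full 20% is lost in follow-up.* The article gives 20% over the whole study. Primary outcome provides for women who withdraw during treatment, and treatment is the demanding phase, with 36 sessions plus ultrasound. Half the loss before Week 12 roughly halves the bias; with three quarters before Week 12, the opposite-direction bias is −0.04 to −0.07 SD.
- *The analysis would yield false claims of lasting benefit.* The raised false-positive rate needs poor responders to leave sham while good responders leave active, and nothing in the article points to that. Participants are to be blinded, so dropout alike in both arms is at least as natural, and it gives about zero bias (0.02 to 0.04 SD too small for a true 0.50 SD). In the opposite-direction pattern the bias runs against acupuncture: rejections in its favour were at most 0.2%.
- *The plan breaks its ITT commitment.* ITT chiefly means analysing women in the arm assigned, and the available-data rule is stated openly. There is tension over missing data, not a contradiction.

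None of this removes the gain from using a Week 12 value that has already been collected.

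**Conclusion.** The point holds as a modest, cheap improvement to the Week 24 secondary contrasts. The plan names a method that leaves a relevant recorded value unused, while the same section uses a better-suited model for COR.

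With correlations of 0.5 with baseline and 0.6 to 0.8 between visits, a joint model gives about a 1% to 7% smaller SE under random dropout. It removes a bias of about 0.04 to 0.10 SD under sham-only dropout of poor responders, and of 0.07 to 0.20 SD, against acupuncture, in the opposite-direction worst case. The lower ends assume half the loss falls before Week 12. If dropout depends on Week 12 alike in both arms, the bias is about zero. The correlations, the timing of loss and the dropout patterns are all assumptions. A joint model cannot recover women lost before Week 12. Sample size and the primary conclusion do not change.

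**What to change.** In Statistical analysis, replace the ANCOVA sentence with one mixed model for repeated measures for each continuous secondary outcome that has a baseline and both later visits:

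- fixed terms for group, visit, group-by-visit, baseline, baseline-by-visit and centre;
- unstructured within-woman covariance;
- all women with at least one post-baseline value.

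Report the Week 12 and Week 24 group contrasts from that model and keep the available-data ANCOVA as a supporting analysis. For PGIC, which has no baseline in Table 1, leave out the baseline terms; the baseline-adjusted ANCOVA does not fit it as written in any case.

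The cost is a sentence in the protocol and a little extra modelling, in the software and with the type of model already planned for COR. The new analysis relies on data being missing at random given the Week 12 value as well as baseline and arm, which is a weaker assumption than the Week 24 ANCOVA makes. The change should be made before outcome data are seen, so that the choice of method cannot depend on results.
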